### Measurements

#### Baseline information

We will record demographic and morphometric data including age, sex, height, weight, American Society of Anesthesiologists (ASA) physical status and medical history (cardiovascular, pulmonary, neurological, presence of diabetes type 1 and type 2, insulin use and alcohol and tobacco use). We will record the home medication (beta-blockers, ACE inhibitors/angiotensin-1 blockers, diuretics, statins, thienopyridines, anticoagulants, insulin or orally administered antidiabetic drugs, alpha-2 agonists/antagonists). We will perform blood samples to measure baseline values in all patients including NT-proBNP, TnT (high-sensitivity, fifth-generation TnT), hemoglobin, inflammatory parameters, thrombocytes, coagulation parameters, electrolytes, creatinine, albumin, liver tests and copeptin. Blood samples for NT-proBNP and oxidation-reduction will be drawn five times (preoperatively, within 2 h after surgery, on the first and third PODs and within 3 days of discharge). Blood samples for TnT and vWF will be drawn four times (preoperatively, within 2 h after surgery, on the first and third PODs).

All laboratory value will be analyzed at the Department of Laboratory Medicine at the Medical University of Vienna.

#### Perioperative data

Intraoperative data, such as end-tidal sevoflurane concentration, anesthetic agents used, medication, fluid balance, amount and start of vasopressor administration, temperature, hemodynamic and respiratory parameters (cardiac output, stroke volume and corrected flow time (FTc), FiO_2_ and end-tidal CO_2_ will be extracted from the electronic anesthesia information management system. Blood-gas analysis (oxygen partial pressure (pO_2_), CO_2_, hemoglobin, pH, base excess), will be performed hourly during surgery and also recorded.

#### Follow-up

Patients will be followed up for the primary and secondary outcome within 2 h after surgery, on POD 1, POD 3 and within 3 days before discharge. Laboratory measurements for outcome assessments are shown in Table 1. We will further perform a telephone follow-up on the 30th day after surgery to evaluate cardiac events including acute heart failure, myocardial infarction and new onset of atrial fibrillation (Table 2). All follow-up measurements will be performed by an investigator who will be unaware of the randomized allocation. Acute heart failure will be defined as cardiac failure needing medical intervention including therapy with inotropes and extracorporeal membrane oxygenation. Myocardial infarction will be diagnosed according the fourth definition of myocardial infarction [21]. Atrial fibrillation will be diagnosed according to the management guidelines for atrial fibrillation [22].

**Table 2 Tab2:** Schedule of study events

Timepoints		Study period						
	Enrollment	Intervention			Postoperative period			Close out
	Preoperative visit	Before anesthesia	During surgery	End of surgery for 2 h after surgery	POD 1	POD 3	Hospital discharge	POD telephone follow-up
***Enrollment***								
Eligibility screening	X							
Informed consent	X							
Patient history	X							
Allocation		X						
***Intervention***								
80% inspired oxygen			X					
30% inspired oxygen			X					
Anesthesia/surgery variables			X					
80% via face mask				X				
30% via face mask				X				
Adverse events			X	X				
***Assessments***								
Outcomes (see Table 1)					X	X	X	
Adverse events					X	X	X	X

Key: *POD* postoperative day

#### Data analysis

Randomized groups will be compared for balance in patient characteristics, demographic data, type of surgery, duration of surgery and anesthesia and preoperative baseline laboratory values (including: NT-proBNP, TnT, hemoglobin, hematocrit, leukocytes, thrombocytes, prothrombin time, activated prothrombin time, sodium, potassium, calcium, magnesium, creatinine, albumin, transaminases, C-reactive protein). The primary analysis will be intention to treat so that all randomized patients will be included in all analyses.

The primary outcome, the effect of 80% versus 30% oxygen on postoperative maxNT-proBNP will be compared using a two-sample, two-tailed Mann-Whitney *U* test. If a patient dies before NT-proBNP on POD 3 is measured, the patient’s maxNT-proBNP will be set to the maximum maxNT-proBNP values over all patients. Multiple imputation will be used for missing postoperative measurements.

Our secondary outcomes including Myocardial Injury after Noncardiac Surgery (MINS) (defined as absolute change of high-sensitive TnT of 5 ng/L between 20 to < 65 ng/L) [23], surgical stress, redox stress and perioperative hemodynamic (fluid and vasopressor requirements) will be analyzed using a two-sample, two-tailed Mann-Whitney *U* test. The exploratory outcomes including cardiac failure, myocardial infarction, acute heart failure requiring intervention, new onset of cardiac arrhythmias and unplanned ICU admission will be analyzed using Kaplan-Meier curves assessed with a log-rank test (Table 1).

If hospital discharge occurs before the third POD, the maximum value of the available data will be used for outcome measure.

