**Methods/design:**

We will conduct a single-center, double-blinded, randomized trial at the Medical University of Vienna, including 260 patients with increased cardiac risk factors undergoing moderate- to high-risk noncardiac surgery. Patients will be randomly assigned to receive 80% versus 30% oxygen during surgery and for 2 h postoperatively. The primary outcome will be the difference in maximum NT-proBNP release after surgery.

As secondary outcomes we will assess the effect of supplemental oxygen on postoperative maximum troponin T concentration, oxidation-reduction potential, von Willebrand factor concentration and perioperative fluid requirements. We will perform outcome measurements 2 h after surgery, on postoperative day 1 and on postoperative day 3. The NT-proBNP concentration and the oxidation-reduction potential will also be measured within 72 h before discharge.

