## Methods/design: data collection, management and analysis

### Objectives and design

We will conduct a single-center, double-blinded, two-arm trial at the Medical University of Vienna. In total, we will randomly assign 260 patients to receive 80% versus 30% inspired oxygen concentration for surgery and for 2 h postoperatively. We will follow the Standard Protocol Items: Recommendations for Interventional Trials (SPIRIT) recommendations for interventional trials (Additional file 1). The study was approved by the Ethics Committee of the Medical University of Vienna on 13 November 2017. This trial was registered at ClinicalTrials.gov on 8 December 2017 (NCT03388957) and at the European Clinical Trial Database (2017–003714-68).

This trial will test the primary hypothesis that supplemental oxygen significantly decreases the maximal postoperative NT-proBNP concentration (assessed within 2 h after surgery, on POD 1 and POD 3) in patients with increased cardiovascular risk factors undergoing moderate- to high-risk abdominal surgery.

Our secondary outcomes are differences in maximum TnT concentration, static oxidation-reduction potential (sORP) and oxidation-reduction potential capacity (cORP), as well as vWF values and the perioperative fluid requirements to reach hemodynamic stability (Table 1).

**Table 1 Tab1:** Outcomes assessment

	Outcomes	Measurements
Primary	Myocardial function	maxNT-proBNP
Secondary	MINS	maxTnT
	Surgical stress	Copeptin
	Redox stress	sORP, cORP
	Hemodynamic	
Exploratory	Cardiac failure	50% increase in NT-proBNP
	Myocardial infarction	ECG change and elevated heart-specific enzymes
	Heart failure requiring intervention	50% NT-proBNP increase and medical treatment
	New onset of cardiac arrhythmias	ECG changes requiring medical treatment and/or electric cardioversion
	Unplanned ICU admission	

c*ORP* oxidation-reduction capacity, *ECG* electrocardiogram, *ICU* intensive care unit, *maxNT-proBNP* maximal *N*-terminal pro-B-type natriuretic peptide, *maxTnT* maximal troponin T, *MINS* Myocardial Injury after Noncardiac Surgery, *sORP* static oxidation-reduction potential

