#### Sample size consideration

A previous study showed a nearly 40% reduction of BNP levels in patients with congestive heart failure receiving nocturnal oxygen therapy [12]. Based on our own data of a previous trial (unpublished data) we observed a fourfold increase of BNP (preoperative 129.05 ng/L ± 160.13 to up to 482.49 ng/L ± 538.78) in the postoperative period in relatively healthy patients undergoing moderate- to high-risk open abdominal surgery. We calculated a needed sample size of 254 patients (127 patients per group) to show a 40% reduction of NT-proBNP in patients receiving 80% versus 30% oxygen with a power of 80% at a 0.05 significance level. We will thus include 260 patients (130 patients per group) to compensate for potential drop outs.

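### The primary Mann-Whitney test is valid but leaves the preoperative NT-proBNP, measured in every patient, out of the comparison; adjusting for it would add precision at no data cost

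*Protocol article*

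**What the plan says.** - **Outcome.** Objectives and design gives the primary hypothesis: "supplemental oxygen significantly decreases the maximal postoperative NT-proBNP concentration (assessed within 2 h after surgery, on POD 1 and POD 3"). The variable is an absolute postoperative maximum, not a change from baseline. The abstract's wording is looser: "The primary outcome will be the difference in maximum NT-proBNP release after surgery".
- **Primary test.** Data analysis: "postoperative maxNT-proBNP will be compared using a two-sample, two-tailed Mann-Whitney" U test. No covariate, change score or adjusted supporting analysis is named. A patient who dies before the day 3 sample takes the highest value seen in any patient.
- **Baseline.** Baseline information: "We will perform blood samples to measure baseline values in all patients including NT-proBNP". The NT-proBNP samples are "drawn five times (preoperatively, within 2 h after surgery, on the first and third PODs and within 3 days of discharge").
- **Use of baseline.** Data analysis: "Randomized groups will be compared for balance in patient characteristics", with preoperative NT-proBNP in the list. No other use in comparing the arms is stated.
- **Randomisation.** Assignment to intervention describes permuted blocks of 6 and names no stratification factor.
- **Sample size.** 127 per group, raised to 130, "to show a 40% reduction of NT-proBNP in patients receiving 80% versus 30% oxygen", with 80% power at the 0.05 level. The stated values are 129.05 (SD 160.13) ng/L before and 482.49 (SD 538.78) ng/L after surgery.

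**The concern.** A preoperative value of the same analyte is the obvious prognostic covariate for a postoperative value. In the plan's own earlier data the preoperative SD exceeds the mean, so patients differ widely before any oxygen is given. To the extent that this carries into the postoperative maximum, an unadjusted test treats it as noise although it was measured before the intervention. Neither the described randomisation nor the described analysis removes it.

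What is at stake is sensitivity to effects smaller than 40%. The 40% is supported by a study of nocturnal oxygen in congestive heart failure, and the Background says that no data exist on this question, so a smaller true effect is quite possible. A chance difference in baseline would also make an unadjusted result harder to interpret, and the plan does not say what follows if the balance check shows one.

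**Working it through.** **1. The plan's own figure.** Difference 0.4 × 482.49 = 193.0 ng/L; SD 538.78; two-sided 0.05; power 80%; no covariate.

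n per arm = 2 × [538.78 × (1.960 + 0.842) / 193.0]² = 122.3, so 123 (246 in total). The t distribution gives 124 (248). Dividing 122.3 by the Mann-Whitney relative efficiency of 0.955 gives 128.1, so 129 (258). The stated 254 lies between these. It is consistent with an absolute mean difference and the unadjusted postoperative SD.

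**2. Effect of adjustment on that scale.** Adjusting for a baseline with correlation r multiplies the variance by (1 − r²). The documents do not give r; 0.3, 0.5 and 0.7 are assumptions. The required n per arm falls from 123 to 112, 92 and 63. Power at 127 per arm rises from 81% (about 80% for Mann-Whitney) to 85%, 91% and 98%.

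**3. Log-normal model.** With an SD above the mean, a log scale is more realistic. Log SD = √ln(1 + CV²).
- After surgery: CV = 538.78/482.49 = 1.117, log SD 0.900.
- Before surgery: CV = 160.13/129.05 = 1.241, log SD 0.965.

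The unadjusted standard error of the log difference with 130 per arm is 0.900 × √(2/130) = 0.112. Adjusted, it is 0.112 × √(1 − r²) = 0.106, 0.097 and 0.080. The interval is therefore narrower by 1 − √(1 − r²), or about 5%, 13% and 29%.

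**4. Simulated power, 130 per arm, true 25% reduction.**

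| Assumed r | Mann-Whitney | Rank ANCOVA | Log-ANCOVA |
|---|---|---|---|
| 0.3 | about 70% | 72% | 74% |
| 0.5 | about 70% | 83% | 84% |
| 0.7 | about 70% | 92% | 94% |

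A separate simulation at 127 per arm (4000 trials per setting) gave 73%, 81% and 93% for rank ANCOVA and 76%, 83% and 95% for log-ANCOVA. The figures should be read to within 2 or 3 percentage points. In that simulation:
- true 20% reduction: Mann-Whitney about 49%, rank ANCOVA 53%, 59% and 75%;
- true 40% reduction: Mann-Whitney about 99%, rank ANCOVA above 99%;
- no effect: false-positive rates of 4.5% to 5.6% for all three tests.

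With 2% deaths assumed and held at the worst rank, a 25% reduction gives 67% for Mann-Whitney against 77% to 89% for rank ANCOVA (r = 0.5 to 0.7, 130 per arm).

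**5. Chance imbalance.** One SD of the difference in mean log baseline is 0.965 × √(2/130) = 0.120, about 13% in geometric mean. It moves the unadjusted log outcome difference by r × 0.112, which is 0.056 at r = 0.5 and 0.078 at r = 0.7 (about 6% and 8% on the ratio scale). This is already inside the standard error in step 3: 0.112² = r² × 0.112² + (1 − r²) × 0.112². Given a baseline difference of 1.96 standard errors, the false-positive rate of an unadjusted test is about 13% (r = 0.5) or 21% (r = 0.7). Given a difference of one standard error it is 4.8% or 3.9%. Over all randomisations it is 5%.

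**The case against.** The case for leaving the plan alone is substantial.

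- **The test is valid and conventional.** It holds its 5% error rate, copes with skewed data and suits the worst-value rule for deaths. All of this stands. A reader might infer that chance imbalance biases the trial. It does not: step 5 shows that it is a component of the sampling variance, so it is the same loss of precision and not a second defect.
- **The planned effect is covered.** A reader might infer that the trial is underpowered. The documents do not support that. For a 40% reduction the unadjusted test reaches about 80% on the plan's additive scale and about 99% under the log-normal model.
- **The gain rests on an unknown correlation.** At r = 0.3 it is only 2 or 3 percentage points for rank ANCOVA. The SDs come from relatively healthy patients, and the source text says BNP where the outcome is NT-proBNP. Both limits stand.
- **A percent reduction remains possible.** One might claim that a Mann-Whitney analysis cannot give one with an interval. A Hodges-Lehmann shift on log values, back-transformed, would do so, and the choice of accompanying estimate may sit in an analysis plan that is not shown.
- **The abstract's mention of release** might suggest that the wrong variable is tested. The Background and the Objectives and design section both define the outcome as the maximal postoperative concentration, which is what the test compares.
- **An analysis plan may add an adjusted analysis.** It may, but the protocol article itself names the unadjusted test as primary, so this is a stated choice and not an omission.

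**Conclusion.** The point holds as one of efficiency. The protocol article fixes a valid primary test that makes no use of a baseline value measured in every patient. Under the log-normal model, with 130 per arm and a true 25% reduction, this costs about 2, 13 and 22 percentage points of power against rank ANCOVA at correlations of 0.3, 0.5 and 0.7 (70% against 72%, 83% and 92%). At 40% the cost is negligible under that model. The sizes depend on the assumed correlation and on SDs from a different population.

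The imbalance issue is conditional, not systematic, bias and belongs to the same loss of precision. The documents do not support calling the primary result invalid, biased or underpowered for its stated target. The change is worth making because it costs almost nothing, not because the planned analysis is wrong.

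**What to change.** Before unblinding:

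1. Make the primary test either rank ANCOVA or a proportional-odds model of maxNT-proBNP on arm and preoperative NT-proBNP (ranked or logged, respectively). Name one in advance. Both keep deaths at the worst rank, and the proportional-odds model is the covariate-adjusted counterpart of the Mann-Whitney test.
2. Keep the unadjusted Mann-Whitney test as a sensitivity analysis.
3. Report a baseline-adjusted ratio of geometric means with 95% CI from log-scale ANCOVA as a supporting estimate. State how deaths are handled in it, since an assigned maximum is harmless in ranks but arbitrary on a log scale.
4. Do the same for maxTnT, which also has a preoperative sample.

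No new data are needed; the cost is analysis wording and a few lines of code. It is nevertheless a change to a published primary test, and Trial status says that recruitment ended in December 2019, so it must be documented and dated. The article does not say whether the data are still blinded. If they are not, leave the Mann-Whitney test as primary and report the adjusted analysis as supportive.

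### The MINS definition stops at 65 ng/L, so the largest troponin rises are not cases as written, and the plan does not settle whether MINS or maximum TnT is tested

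*Protocol article*

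**What the plan says.** The statements about troponin in the protocol article do not fit together.

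- **Data analysis** lists MINS first among the secondary outcomes, "defined as absolute change of high-sensitive TnT of 5 ng/L between 20 to < 65 ng/L", citing reference 23. The same sentence says that these outcomes "will be analyzed using a two-sample, two-tailed Mann-Whitney" U test.
- **Objectives and design** states the aim differently: "Our secondary outcomes are differences in maximum TnT concentration", followed by the redox, vWF and fluid outcomes. The Abstract also names maximum troponin T.
- **Table 1** puts MINS in the outcome column and maxTnT in the measurement column.
- **Baseline information** gives the sampling: "Blood samples for TnT and vWF will be drawn four times" (before surgery, within 2 h after it, and on postoperative days 1 and 3).
- **Follow-up** handles infarction separately: "Myocardial infarction will be diagnosed according the fourth definition of myocardial infarction". Table 1 lists it as exploratory and requires ECG change plus raised enzymes.

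No section adds a category for troponin at or above 65 ng/L.

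**The concern.** An injury outcome should not switch off at the highest injury. The written rule has an explicit ceiling, so the patients with the largest rises fall on the non-case side. The population is selected for cardiac risk (Study population), so values above the ceiling are plausible.

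The second problem is which variable the test applies to. A threshold definition produces a yes/no variable, whereas maximum TnT is continuous. If maximum TnT is what is tested, the MINS definition has no stated use. If MINS is what is tested, its definition leaves out the worst cases.

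Both directions of effect are live in this trial. The Background cites a post-hoc signal of more infarction with supplemental oxygen, and the Discussion cites a 30% reduction in a composite that includes myocardial injury. A capped count could mislead about either.

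**Working it through.** **No plan figure to reproduce.** The article gives no MINS rate, effect size or power. Its only calculated figure is the 254 patients for NT-proBNP. A t-test with difference 0.4 × 482.49 = 193.0 and SD 538.78 gives 124 per group (248), close to the stated 127. Nothing below depends on that figure. The planned 130 per arm is used for illustration.

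**Step 1: the rule applied literally.** From 10 to 40 ng/L: change 30, value inside 20 to <65, so a case. From 10 to 300 ng/L: change 290, value outside the band, so not a case.

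**Step 2: how many patients the cap could affect.** Assume postoperative TnT is log-normal with median m and log-SD s. These values are assumptions, and the 5 ng/L change criterion is not modelled.

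- Share at or above 65 = 1 − Φ((ln 65 − ln m)/s).
- m = 14, s = 1.0: 6.2% of patients, which is 0.17 of those at 20 ng/L or more.
- m = 20, s = 1.0: 11.9%, or 0.24.
- m = 20, s = 1.2: 16.3%, or 0.33.
- Of 260 patients: 0.062 × 260 ≈ 16 to 0.163 × 260 ≈ 42.

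**Step 3: what the cap does to a treatment effect.** Band share = Φ((ln 65 − ln m)/s) − Φ((ln 20 − ln m)/s). For a harmful 1.5-fold shift in one arm:

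| Control median, log-SD | Band 20 to <65 | All values ≥20 |
|---|---|---|
| 14, 1.0 | 29.8% → 39.0% (+9.2) | 36.1% → 51.9% (+15.8) |
| 20, 1.0 | 38.1% → 43.8% (+5.7) | 50.0% → 65.7% (+15.7) |
| 20, 0.8 | 43.0% → 52.7% (+9.7) | 50.0% → 69.4% (+19.4) |
| 30, 0.8 | 52.7% → 52.2% (−0.5) | 69.4% → 84.5% (+15.1) |
| 40, 0.8 | 53.5% → 45.5% (−8.0) | 80.7% → 91.5% (+10.8) |

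**Step 4: when the direction reverses.** On the log scale the band share is symmetric about √(20 × 65) = √1300 ≈ 36 ng/L. With equal log-SD it falls only when the product of the two medians exceeds 1300. From median 20 the shift must exceed 1300/20² = 3.25-fold. From median 14 it must exceed 1300/14² ≈ 6.6-fold. From median 40 any upward shift lowers it.

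**Step 5: simulation** (4,000 trials, 130 per arm, log-SD 0.8, 1.5-fold harm). The harmed arm had the lower band rate in 5% of trials at control median 20, 53% at 30 and 88% at 40. At median 20 the band count detected harm at the 5% level in 35% of trials. Mann-Whitney on maximum TnT detected it in about 98% at every median.

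**Step 6: a reversal in counts (invented, to show the mechanism only).** 80% arm: 20 in band, 20 at 65 or more. 30% arm: 32 in band, 5 at 65 or more. Band only: 20/130 = 15.4% against 32/130 = 24.6%, ratio 0.63. With the high values counted: 40/130 = 30.8% against 37/130 = 28.5%, ratio 1.08.

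**The case against.** The strongest reply is that no section plans a count of MINS. The stated test is a rank test, Table 1 gives maxTnT as the measurement, and the objectives name maximum TnT. On that reading a patient at 300 ng/L ranks at the top and nothing is lost. This stands: a rank test on maximum TnT is not harmed by the cap. It does not explain why a threshold definition appears in the sentence that assigns the test.

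A reader might infer that the cap would make a harmful effect look protective. The documents do not support that as a general claim. They give no troponin distribution, and at assumed medians of 14 to 20 ng/L the harmful shift would have to exceed roughly 3.25-fold to 6.6-fold.

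The missing branch may be a shortening of reference 23, which is not shown, or the band may only mark where the change rule applies. Either is possible. Even so, the printed rule is a complete statement with a ceiling, not a detail left for later, and it gives the wrong answer when applied.

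Infarction is separately defined and adjudicated blind, so major events are not lost. This also stands, but Table 1 requires ECG change for infarction, and MINS is not on the adjudication list. Large troponin rises without ECG change are therefore not picked up there.

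Finally, a Mann-Whitney test on a yes/no variable with tie correction is a valid test of proportions, and an article need not name a risk ratio. Both points are fair. Writing a change of 5 rather than at least 5 is a minor wording matter.

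**Conclusion.** The point holds in limited form. As written, MINS excludes patients at 65 ng/L or more, and the article does not settle whether MINS or maximum TnT is tested.

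If MINS is counted as yes/no, the cap would misclassify about 6% to 16% of patients under the assumed distributions. It would typically shrink a treatment effect: for a 1.5-fold shift at medians 14 to 20, the difference falls from about 16 to 19 percentage points to about 6 to 10. Reversal is confined to settings where many patients lie near or above 65 ng/L, such as an assumed median of 40.

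All these sizes rest on assumed log-normal troponin without the change criterion. The misclassification itself follows from the wording alone. Maximum TnT analysed by ranks, the primary outcome and the sample size are untouched. This should be fixed, but it does not threaten the trial's main conclusion.

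**What to change.** In Data analysis and Table 1:

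1. Remove the upper limit from the MINS definition so that values of 65 ng/L or more count as MINS. Check the exact wording against the definition cited as reference 23.
2. State the change criterion as at least 5 ng/L.
3. List MINS as a yes/no outcome and compare it between arms as a proportion.
4. List maximum TnT separately as the continuous secondary outcome tested by Mann-Whitney U, in line with the objectives.

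The cost is a line or two of text. Trial status reports recruitment complete, but the four planned troponin samples already supply what is needed. The change is best made and dated before troponin is compared by arm.

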### Assignment to intervention

Given an average estimated recruitment rate of 10 patients per month, we anticipate a recruitment period of 25 months. A trained study coordinator will evaluate eligibility and obtain informed consent. All patients will be recruited using the operation schedule the day before surgery. After meeting the eligibility criteria, the inclusion criteria will be checked. Two copies of the signed consent form will be made. One copy remains in the patient chart, and the second one will be given to the patient. On the consent form, participants will be asked if they agree to the use of their data should they choose to withdraw from the trial. Participants will also be asked for permission for the research team to share relevant data with people from the Universities taking part in the research or from regulatory authorities, where relevant. This trial does not involve collecting biological specimens for storage.

On the day of surgery the coordinator will enroll the participants via accessing the web-based system. We will use permutated block randomization using a web-based randomization program (Randomizer, Medical University of Graz, Graz, Austria). Each block has a size of 6 numbers, randomly ordered to the two treatment assignments, of which all investigators were unaware. The web-based randomization program was set up by an investigator not involved in data acquisition. Intraoperative investigators and clinicians will be not blinded to the allocated treatment group. However, an observer strictly blinded to the group assignment will evaluate complications during hospitalization. Subsequently, a blinded investigator will call all patients 30 days after surgery and to evaluate outcomes.

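### Kaplan-Meier does not suit cardiac failure defined by an NT-proBNP rise, which is visible only at in-hospital draws: compare proportions instead

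*Protocol article*

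**What the plan says.** The Data analysis section places cardiac failure, myocardial infarction, heart failure requiring intervention, arrhythmias and unplanned ICU admission under one sentence: "new onset of cardiac arrhythmias and unplanned ICU admission will be analyzed using Kaplan-Meier curves assessed with a log-rank test".

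Table 1 defines cardiac failure as a "50% increase in NT-proBNP". It defines heart failure requiring intervention as the same rise plus medical treatment.

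Under Baseline information, the postoperative NT-proBNP draws are "within 2 h after surgery, on the first and third PODs and within 3 days of discharge". None is planned after discharge.

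The places that bear on how long the other outcomes are followed do not fully agree:
- Follow-up describes a "telephone follow-up on the 30th day after surgery to evaluate cardiac events including acute heart failure, myocardial infarction and new onset of atrial fibrillation". Unplanned ICU admission is not named, but the list is open-ended.
- In Table 2 the row "Outcomes (see Table 1)" is marked at POD 1, POD 3 and hospital discharge and is blank at the telephone call. Adverse events are marked at the call.
- Assignment to intervention says that "an observer strictly blinded to the group assignment will evaluate complications during hospitalization", and then that "a blinded investigator will call all patients 30 days after surgery and to evaluate outcomes".

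The article gives no time origin, horizon or censoring rule for these outcomes.

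**The concern.** Kaplan-Meier treats a censored patient as one who could still have the event later and who shares the future risk of those still observed. For an outcome read from blood drawn in hospital, live discharge ends the possibility of recording the event.

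A second feature is specific to this outcome. After POD 3, each patient who is still negative is tested once, on a day set by that patient's discharge. A late positive is then divided by the number of patients not yet discharged, and that number shrinks towards one. Each late positive therefore takes a growing step off the curve.

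The stake is descriptive. A reader would take the height of the curve as the share of patients with cardiac failure in that arm. It would instead be a larger number that depends on length of stay.

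**Working it through.** **Figures in the plan.** The article gives no event rate, length of stay or censoring share for these outcomes, so there is no stated figure to reproduce. The sample size of 254 concerns the primary outcome and has no bearing here. The usable inputs are 130 patients per group and the pilot BNP values, 129.05 ± 160.13 before and 482.49 ± 538.78 ng/L after surgery (Sample size consideration).

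**How many would be positive by POD 3?** Fit log-normals to the pilot values.
- Log variances: ln(1 + (160.13/129.05)²) = 0.932 and ln(1 + (538.78/482.49)²) = 0.810.
- Log means: ln 129.05 − 0.932/2 = 4.394 and ln 482.49 − 0.810/2 = 5.774, a difference of 1.380.
- P(rise above 50%) = Φ[(1.380 − ln 1.5)/SD of the log difference]. With an assumed correlation of 0.3 to 0.85 this is 81-97%.
- With a 40% reduction (add ln 0.6 = −0.511) it is 66-82%.

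A range of 70-90% is therefore reasonable.

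**Assumptions.** Stay is log-normal, median 9 days, log-SD 0.5, rounded to days, with nobody leaving before day 4. A share p is positive by POD 3. Each remaining patient has probability q of first crossing the threshold at the pre-discharge draw, taken on the day of discharge, and is otherwise censored that day.

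**Formulas.**
- True proportion = p + (1 − p)q.
- On day u, d of the n patients still negative and in hospital leave, so the expected Kaplan-Meier factor is 1 − q·d/n. The product over days is close to S(t)^q, where S(t) is the share of stays longer than t. Hence 1 − KM(t) ≈ 1 − (1 − p)·S(t)^q.

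**Middle scenario (p = 80%, q = 10%).**
- True: 0.80 + 0.20 × 0.10 = 82.0%.
- Day 14: S = 1 − Φ[ln(14.5/9)/0.5] = 0.170, and 0.170^0.1 = 0.838. So 1 − KM = 1 − 0.20 × 0.838 = 83.2%, which is 1.2 points above the final true proportion.
- End of curve (simulation, 3,000 trials of 130 patients): 86.1%, an excess of 4.1 points. The standard error of a proportion is √(0.82 × 0.18/130) = 3.4 points, so the excess is about 1.2 SE.

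**Range at the end of the curve, same simulation.**

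| Positive by POD 3 | Late conversion | True | 1 − KM | Excess (points) |
|---|---|---|---|---|
| 90% | 5% | 90.5% | 91.4% | 0.9 |
| 90% | 10% | 91.0% | 92.6% | 1.6 |
| 80% | 5% | 81.0% | 83.3% | 2.3 |
| 80% | 10% | 82.0% | 86.1% | 4.1 |
| 70% | 5% | 71.5% | 75.4% | 3.9 |
| 70% | 10% | 73.0% | 80.0% | 7.0 |

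With q = 0 the excess is zero in every row. A separate simulation (260 patients, median stay 5, 7 or 10 days, draw up to 3 days before discharge, some discharges before POD 3) gave about 2 to 6 points with 5-10% late conversion and 0 to 0.5 without. If event-free patients are carried to a fixed horizon, 1 − KM equals the crude proportion every time.

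**Log-rank.** With equal event hazards and 130 per arm, the test rejected in 4.7-5.8% of trials, including mean stays of 10 versus 7 days. With the discharge-timed draw, 80-90% positive by POD 3 and unequal stays, it rejected in 3.5-6.1%. The highest value was 8.5%, in an extreme case (50% by POD 3, 20% late, stays of 10 versus 7 days).

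**Unplanned ICU admission, if seen only in hospital.** The size depends on timing.
- Early events (mean day 2; median stay 7 or 10 days): true 4.6% reads 4.9%, and true 4.9% reads 5.0%.
- Constant hazard, true 5% by day 30, mean stay 10 days: an event hazard h = 0.0055 per day gives h/(h + 0.1) × [1 − exp(−30(h + 0.1))] = 5.0%, while 1 − exp(−30h) = 15.2%. Mean stays of 7 and 14 days give 20.4% and 11.9%.

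**The case against.** The strongest reply is that discharge censoring is inferred. The article states no censoring rule or horizon, and a condensed article may leave both to the analysis plan. Timing events by scheduled visit, or carrying event-free patients to day 30, removes the excess. This stands as far as it goes: a reader might infer that the plan orders censoring at discharge, and it does not. But both escapes return exactly the crude in-hospital proportion. The named method is then either misleading for this outcome or a roundabout way to a number that could be named directly.

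Other parts of the reply also stand:
- A reader might infer that the log-rank comparison is invalid. The simulations do not support that.
- A reader might infer that unplanned ICU admission is captured only in hospital. Table 2 and the Follow-up list point that way, but the list is open-ended and the day-30 call is said to evaluate outcomes, so this is not settled.
- Stay and late-conversion rates have no source in the article. Excesses near 20 points need only 50% positive by POD 3, below what the pilot values suggest.
- The excess builds up in the tail of the curve, after most patients have left.

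**Conclusion.** The point holds for cardiac failure defined by NT-proBNP, and for the NT-proBNP part of heart failure requiring intervention. Neither can be observed after discharge on any reading. Under ordinary censoring at the last in-hospital observation, the curve would overstate the proportion affected by about 1 to 7 points at its end, for 70-90% positive by POD 3 and 5-10% late conversion. It would overstate by about 1 point at day 14 in the middle scenario, and not at all without late conversion. These sizes rest on the assumed stay distribution.

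The log-rank test is roughly valid for in-hospital hazards but does not answer how many patients were affected. For unplanned ICU admission the text needs reconciling before any bias can be claimed.

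It would go too far to conclude that the trial's answer on cardiac benefit or harm is compromised. These outcomes are exploratory, and the primary Mann-Whitney comparison is untouched.

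**What to change.** In Data analysis:
1. Compare NT-proBNP-defined cardiac failure between arms as a proportion, with a risk difference or risk ratio and 95% CI. Base it primarily on the fixed 2 h, POD 1 and POD 3 draws, and report the pre-discharge draw in addition. The fixed draws matter because a proportion that includes a discharge-timed draw can itself vary with length of stay.
2. Reconcile Follow-up, Table 2 and Assignment to intervention on whether unplanned ICU admission is ascertained to day 30. If it is seen only in hospital, report an in-hospital proportion, or cumulative incidence with live discharge and death as competing events.
3. Reconcile the heart failure definition in Table 1, which requires an NT-proBNP rise, with the clinical definition under Follow-up.
4. Keep Kaplan-Meier and log-rank only for outcomes ascertained to day 30 in every patient, and state that discharge is not a censoring time.

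The cost is wording, plus a decision on definitions and ascertainment under items 2 and 3. No extra samples, visits or patients are needed. The affected exploratory outcomes lose their time-to-event display.
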